## Abstract

**Background:**

Enteral nutrition (EN) is preferred when oral feeding is not possible. The use of the Nasogastric Tube (NGT) ensures rapid and low-risk nutrient administration. However, confirming the placement through chest radiography, besides delaying the initiation of nutritional therapy, exposes patients to radiation. The pH test of gastric aspirate provides a quicker check for NGT placement, but its reliability is compromised by challenges related to aspirating gastric secretions.

**Study objective:**

The main objective of this study is to assess the high-performance placement of NGTs for nutritional purposes, optimizing the evaluation of correct insertion through pH testing using an electronic pH meter. Additionally, the study aims to evaluate patient tolerance to the intervention.

**Materials and methods:**

This single-center RCT will include 150 EN candidate patients divided into three groups. Each group will use distinct NGTs, evaluating placement through pH testing and chest radiography for safety. Tolerance, complications related to NGT placement, and costs will be assessed, with data collected anonymously through a secure electronic database.

**Ethical considerations:**

authorization no. 3624, Territorial Ethical Committee Lombardy 5, October 20, 2023.

**Implications and perspectives:**

This protocol introduces innovative technologies, such as advanced NGTs and an electronic pH meter, aiming to optimize enteral nutrition management. This RCT focuses on replacing X-rays as the primary method for verifying NGT placement, thereby reducing costs, time, and patient exposure to radiation. Data analysis may provide insights into managing patients on pH-altering medication. Implementing innovative technologies has the potential to reduce errors and improve economic efficiency and process sustainability.

## Introduction

1

Hospital malnutrition is a condition characterized by an insufficient intake of nutrients, leading to a compromise in health status and quality of life [1]. It is estimated that in Europe, the prevalence of malnutrition related to acute or chronic diseases in hospitalized patients is around 30 % [1]. Moreover, malnutrition can lead to negative clinical outcomes [2] such as: immune system issues [3], difficulty in wound healing [4], loss of muscle mass [5], longer hospital stays [6], higher hospitalization costs [7], and increased mortality [8]. To prevent and treat hospital malnutrition, it is crucial to assess the risk of nutritional deficiency or the presence of malnutrition during all stages of hospitalization, using validated and standardized screening tools [9]. This not only allows for planning focused on prevention but also early treatment of a potential malnourished state [10]. Additionally, nutrition and hydration are considered primary needs of the patients, directly involving nursing staff in nutritional care at various levels [11]. In light of this, when physiological oral feeding is not possible, enteral nutrition should always be considered as the elective nutritional treatment, not only for the maintenance of gastrointestinal tract homeostasis but also due to the lower risk of complications [12] and reduced costs [13]. Enteral nutrition involves the introduction of food into the digestive system through a nasogastric tube, nasojejunal tube, surgical gastrostomy, or percutaneous endoscopic gastrostomy (PEG) [14,15]. It has shown better clinical outcomes when started early [16], promoting better wound healing [17], improved modulation of the inflammatory response [18], prevention of intestinal atrophy [19], reduction of complications, and decreased mortality [20,21]. The first-line nutritional support commonly used for nutritional purposes is NGT [22]. This medical device, whose placement and management is the responsibility of the nursing staff, is a safe medical device and allows the initiation of enteral nutrition administration in a reduced timeframe [23], depending on the waiting times for a control chest x-ray (current Gold Standard) of individual hospitals to verify its correct placement. Recent studies [24,25] suggest that the evaluation of gastric aspirate using the pH test could be a valid alternative to confirm the placement of the NGT (pH ≤ 5.5). These studies also indicate the opportunity to use digital equipment [26] for such measurement, overcoming the limitations of traditional reactive strips. Indeed, the interpretation of pH using reactive strips could be imprecise [27,28], and this could lead to possible interpretation errors by healthcare professionals. Several studies have shown that the interpretation of pH with the most common reagent strips involves possible biases in distinguishing between pH values of 5.0 and 6.0. Furthermore, pharmacological treatments with antacids and the intake of food could increase gastric pH, leading to possible biases in the obtained result [29,30]. However, considering the indications from a recent study [31], it is necessary to evaluate possible difficulties related to the procedure of aspirating gastric secretions for the pH test. Indeed, as expressed by several authors [32], the use of standard NGTs with a small calibre (8–12 CH) and without a second lumen dedicated to aspiration [32] sometimes involves difficulties in aspirating gastric secretions, increasing the risk of error; in the face of these problems, the use of chest radiography is indicated to confirm correct placement [33,34]. However, chest radiography involves exposure to radiation [[33], [34], [35]], an additional cost, and a delay in the start of feeding or any pharmacological therapy [36]. These delays contrast with the primary objective of feeding through the NGT, which is to improve the nutritional intake of patients at high risk of malnutrition quickly [37].

In the current context, the verification of the correct placement of the nasogastric tube is carried out through a rigorous multidisciplinary protocol. The procedure involves the aspiration of at least 5 ml of gastric secretion and the subsequent evaluation by pH test. In case of the procedure being unsuccessful, the placement is defined through chest X-ray. Based on the collected data, the percentage of patients in whom it was possible to successfully apply this protocol was 42% of all placements performed. This result highlights a limited success rate, largely associated with intrinsic difficulties encountered during the aspiration phase. These difficulties are frequently linked to the current use of nasogastric tubes, demonstrating significant complexity in implementing the multidisciplinary protocol. The data aligns with current scientific literature, indicating potential limitations in the application of this procedure. This could not only compromise nutritional benefits for the patient but also hinder cost optimization from an economic sustainability perspective. To date, existing scientific literature lacks clinical studies addressing the highlighted issues, both in terms of overcoming difficulties in gastric aspiration and adopting the use of electronic pH meters [[38], [39], [40], [41], [42], [43], [44]].

### Study Objectives

1.1

The aim of this study is to evaluate the placement of NGT for nutritional purposes according to the best standards of safety and quality by developing a multidisciplinary protocol for this procedure. Through the use of NGTs that can guarantee greater aspiration performances with the same caliber, it would be possible to have a better aspiration of the gastric aspirate (≥5 ml) which would guarantee the possibility of carrying out the pH test in order to ensure correct positioning of the NGT.

### Primary endpoint

1.2

Evaluate the correct positioning of the NGT for enteral nutrition assuming an aspiration of the gastric aspirate of at least 5 ml in order to be able to carry out the pH test using an electronic pH meter (measurement carried out at the first positioning of the NGT).

Ability of the pH test to identify incorrect positioning of the SNG as well as the result of the chest x-ray. Furthermore, in the event of a doubtful RX result or one that does not identify the correct positioning, the pH test is able to detect the incorrect positioning.

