### Secondary endpoint

1.3

The first secondary outcome to evaluate is the sensitivity/specificity of the pH test compared to the current Gold Standard (chest X-ray), also in consideration of clinical variables such as: food intake (time calculated in minutes from the last food intake, guaranteeing a minimum time to perform the test of at least 1 h) and taking drugs that affect gastric pH (proton pump inhibitors and antacids). Secondly, to evaluate the tolerance of the different NGT models used through pain monitoring (evaluated through the NRS scale at 24-48-72 h after placement and where an NRS score greater than ≥3 will be considered as a threshold value to identify poor tolerance). Thirdly, to evaluate the starting time of nutritional therapy from the request for placement of the NGT by the attending physician (calculated in minutes). Lastly, to evaluate possible complications associated with the positioning of the NGT and arising during the hospitalization period, such as: 1) mispositioning of the NGT (assessed with Chest X-ray); 2) tracheobronchial aspiration; 3) aspiration pneumonia 4) lesions of the oesophageal mucosa and of the upper airways (for points 2,3,4 evaluations by clinical examination, blood tests and instrumental tests requested by the attending physician).

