### Safety outcomes

1.5

At each placement of NGT, a check will be carried out by means of a pH test with an electronic pH meter associated with a chest x-ray in order to evaluate the correct or not correct positioning of the device.

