#### Clinical investigation intervention

2.2.5

*Medical device.* This randomized clinical trial will include three study arms to which patients will be assigned according to the enrolment criteria set out in the research protocol. Each arm of the study will involve a different type of NGT. The types of NGTs are reported in section 1.1. These two NGTs have a single lumen and are made of specific materials that give greater performance. In all three study arms, the determination of the correct positioning (primary outcome) will take place through the monitoring of the gastric pH (gastric aspirate 5 ml; pH value ≤ 5.5) through the use of an electronic pH meter (pH Strips & Reader pH X-act) which will be compared with the chest X-ray (current gold standard).

*Labelling and supply.* All electro medical equipment (pH meter) for this study will be provided free of charge for testing purposes by the respective manufacturers/suppliers, while medical devices (NGTs) will be provided free of charge.

*Storage conditions.* The NGT devices can be kept in the common storage environments used for the principals. A total of two pH metres will be assigned to each ward. The management and storage of the device will be carried out by the analysis laboratory of the structure in which the trial is being performed.

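### Detecting misplaced tubes as well as X-ray is listed as both primary and secondary, and the trial is sized and analysed only for measurable pH

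*Protocol article*

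**What the plan says.** Section 1.2 of the protocol article (Primary endpoint) has two paragraphs. The first concerns correct positioning, "assuming an aspiration of the gastric aspirate of at least 5 ml in order to be able to carry out the pH test" with the electronic meter at first placement. The second adds the "Ability of the pH test to identify incorrect positioning of the SNG as well as the result of the chest x-ray", and then states that "in the event of a doubtful RX result or one that does not identify the correct positioning, the pH test is able to detect the" misplacement.

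Section 1.3 (Secondary endpoint) names as the first secondary outcome "the sensitivity/specificity of the pH test compared to the current Gold Standard (chest X-ray"). Sections 2.2 and 2.2.5 attach the label of primary outcome to correct positioning judged by pH ("gastric aspirate 5 ml; pH value ≤ 5.5") and compared with X-ray.

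Section 2.5.1 calculates the sample size from measurable pH alone: 42% with the standard method against at least 62%, 80% power, 5% type I error, 47 per arm, raised to 50 per arm and 150 in total. The only result that section 2.5.3 ties by name to the primary endpoint is the percentage of placements that allow a pH measurement, with a 95% confidence interval.

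Section 1.5 has every placement checked by a "pH test with an electronic pH meter associated with a chest x-ray". The abstract says: "This RCT focuses on replacing X-rays as the primary method for verifying NGT placement".

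**The concern.** One comparison, pH against X-ray for finding misplaced tubes, is primary in 1.2, 2.2 and 2.2.5, secondary in 1.3, and absent from both the sample size calculation and the named primary analysis. An analysis plan cannot settle this by adding detail, because the protocol's own sections disagree on what the primary endpoint is.

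The error that matters most for relying on pH is a misplaced tube that reads 5.5 or below. Its frequency can be estimated only from misplaced tubes that yield enough aspirate, and the trial was not sized on their number. If 1.2 stands, a result such as 3 of 3 misplaced tubes detected could be reported as a primary endpoint met and quoted in support of replacing X-ray.

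The sentence on doubtful films adds a smaller difficulty. It asserts that the pH test detects misplacement where the reference gives no clear answer, and it names no other reference.

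**Working it through.** **1. The plan's own figure.** Inputs from 2.5.1: p0 = 0.42, p1 = 0.62, power 80%, type I error 5% (taken as two-sided). One-sample test of a proportion, normal approximation:

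n = [(1.96 × √(0.42 × 0.58) + 0.8416 × √(0.62 × 0.38)) / 0.20]² = [(0.967 + 0.409) / 0.20]² = 47.3.

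This agrees with the stated 47 per arm. The figure covers measurable pH and nothing else.

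**2. Misplaced tubes with a pH reading.** Expected number = N × misplacement rate × proportion aspirable. N = 150 is from 2.5.1. The misplacement rate is not in the documents, so it is an assumed range. The 62% is the plan's target for all placements; applying it to misplaced tubes is a second assumption.

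**3. Best case.** If all k such tubes are detected, the exact two-sided 95% lower limit is 0.025^(1/k).

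| Assumed misplacement | Expected tubes, whole trial | Per arm | All detected | 95% lower limit |
|---|---|---|---|---|
| 2% | 150 × 0.02 × 0.62 = 1.9 | 0.6 | 2/2 | 16% |
| 5% | 4.7 | 1.6 | 5/5 | 48% |
| 10% | 9.3 | 3.1 | 9/9 | 66% |
| 20% | 18.6 | 6.2 | 19/19 | 82% |

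At 2% the chance of no informative tube at all is (1 − 0.02 × 0.62)^150 = 15%.

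**4. Sensitivity to the aspiration assumption.** If every misplaced tube gave aspirate, 10% misplacement would yield 15 tubes, and 15/15 has a lower limit of 78%.

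**5. What a 90% lower limit would take.** The smallest k with 0.025^(1/k) ≥ 0.90 is 36, with no miss. At 62% aspirable that is 36 / (0.62 × 0.10) = 581 patients at 10% misplacement, 1,162 at 5% and 2,904 at 2%. The 90% is an illustration; the documents set no target or margin.

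**6. Doubtful films.** Section 1.3 makes X-ray the reference. Section 3 (Implications and Perspectives) says that correctly placed tubes in patients on antacids or PPIs may read above 5.5. A pH above 5.5 beside a doubtful film may therefore be a misplaced tube or a correctly placed tube in a treated patient. The two tests together cannot tell which.

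**The case against.** The strongest reply is that the plan already treats measurable pH as primary in practice, since the sample size and the named analysis both do, so the second paragraph of 1.2 is only loose wording. That limits the repair to wording, but it does not remove the contradiction: 2.2 and 2.2.5 repeat the accuracy comparison under the primary label.

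Four stronger readings are tempting, and the documents do not support them.

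- A reader might infer that the pH test becomes its own reference when the film is doubtful. The sentence is awkward and states an expected ability. No section says that doubtful films enter the accuracy table or that pH decides them, and 1.3, 2.2 and 2.2.5 all keep X-ray as the reference. The sentence is unclear; it is not an adjudication rule.
- A reader might take it as fact that few tubes will be misplaced. Section 1.3 lists mispositioning as a possible complication but gives no frequency. The counts above hold only under the assumed rates.
- A reader might infer that failed aspirations disappear. They are the failures of the measurability endpoint, and 2.5.2 evaluates all randomised patients by intention to treat.
- A reader might infer that the trial sets out to abandon X-ray altogether. Every placement in the trial has one (1.5), section 2.1 speaks of reducing its use, and section 3 keeps it for readings above 5.5. The broad claim comes from the abstract.

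How indeterminate films are tabulated in detail can properly be left to an analysis plan.

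**Conclusion.** The point holds as an endpoint conflict together with an accuracy claim that the design does not support. Misplacement detection has two incompatible ranks and no sample size behind it. Under assumed misplacement of 2% to 20% with 62% aspirable, even perfect detection leaves a lower limit between 16% and 82%. The imprecision persists at the high end of that range, and also at 10% if every misplaced tube gives aspirate (78%), so the conclusion does not turn on one assumed rate. The 47 per arm for measurable pH is not in question. On doubtful films, the conclusion goes no further than this: a high pH beside an indeterminate X-ray must not be counted as a verified detection, and the present wording leaves room for that.

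**What to change.** 1. In 1.2, make measurable pH (at least 5 ml of aspirate at first placement) the sole primary endpoint.
2. Move the second paragraph of 1.2 into the accuracy outcome in 1.3, and align the primary-outcome label in 2.2 and 2.2.5.
3. Report accuracy descriptively, pooled over the three arms, with exact 95% confidence intervals, among patients with a definite X-ray. Report doubtful films separately, and reword the sentence about them so that it claims no detection.
4. Narrow the abstract's claim to how often X-ray might be avoided, and state that the trial is not sized to show that pH testing detects misplacement as well as X-ray.

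The cost is a softer replacement claim and edits to endpoint and analysis wording. No new data are needed, because X-ray is already taken at every placement.

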### Secondary endpoint

1.3

The first secondary outcome to evaluate is the sensitivity/specificity of the pH test compared to the current Gold Standard (chest X-ray), also in consideration of clinical variables such as: food intake (time calculated in minutes from the last food intake, guaranteeing a minimum time to perform the test of at least 1 h) and taking drugs that affect gastric pH (proton pump inhibitors and antacids). Secondly, to evaluate the tolerance of the different NGT models used through pain monitoring (evaluated through the NRS scale at 24-48-72 h after placement and where an NRS score greater than ≥3 will be considered as a threshold value to identify poor tolerance). Thirdly, to evaluate the starting time of nutritional therapy from the request for placement of the NGT by the attending physician (calculated in minutes). Lastly, to evaluate possible complications associated with the positioning of the NGT and arising during the hospitalization period, such as: 1) mispositioning of the NGT (assessed with Chest X-ray); 2) tracheobronchial aspiration; 3) aspiration pneumonia 4) lesions of the oesophageal mucosa and of the upper airways (for points 2,3,4 evaluations by clinical examination, blood tests and instrumental tests requested by the attending physician).

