### Study procedures

2.2

Participants will be enrolled in three study arms, assigned according to the defined randomization criterion, to evaluate three different NGT models along with the use of an electronic pH meter. The first NGT is the *NUTRICIA FLOCARE PUR TUBE CH14 double lumen*, which features an additional lumen to the nutritional lumen specifically for pH aspiration. The other two NGTs are the *INNOVAMEDICA single lumen CH10 AVANOS_ST CH10* and the *INNOVAMEDICA single lumen CH12 AVANOS_ST CH12*, which have a single lumen. In all three study arms, the determination of the correct positioning (primary outcome) will take place through the monitoring of the gastric pH (gastric aspirate 5 ml; pH value ≤ 5.5)^46^ through the use of an electronic pH meter (pH Strips & Reader Innovamedica model pH X-act) which will be compared with the CXR (current gold standard). The comparison with the CXR will allow to evaluate the sensitivity and specificity of the pH test. An important aspect of the study is the evaluation of the time efficiency in starting nutritional therapy. This is measured in minutes and aims to determine if the pH test can reduce the time taken for NGT positioning evaluation compared to the current 1440 min required for chest X-ray assessments. The time frame is obtained from the evaluation of the service at IRCSS Humanitas Research Hospital. Furthermore, Patient tolerance to the NGT will be assessed at 24, 48 72 h post-placement using the NRS scale. This will help identify pain levels and characteristics, to evaluate whether different NGT calibers (CH) affect patient tolerance. Throughout the entire period of hospitalization of the patient, complications associated with the positioning of the NGT will be recorded. These include mispositioning of the NGT (assessed by chest x-ray); tracheobronchial aspiration; aspiration pneumonia; lesions of the oesophageal mucosa and upper airways (assessed by clinical examination and instrumental tests requested by the attending physicians). During the post-clinical phase, an economic analysis will be conducted to evaluate potential cost savings from using the pH test for correct NGT positioning, with respect to X-ray use. This includes analysing costs of auxiliary personnel (based on transport times to radiology, calculated as Euro/hour), professional fees for performing chest Xrays, and the cost of the Xrays themselves. A graphical representation of the study procedures is depicted in Fig. 1.

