#### Compliance with clinical investigation intervention

2.2.7

Correct positioning will be monitored by pH testing with an electronic pH meter and chest X-ray. Any acute complications related to the positioning of the nutritional aid and the patient's tolerance during the period of hospitalization will also be monitored.

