### Return or destruction of the medical device

2.4

As regards the NGT in use, if they are removed after positioning during the hospitalization period, the disposal will be the responsibility of the hospital through the procedure that regulates special hospital waste. The pH meters in use, being supplied free of charge by the distributing company, will be returned at the end of this study.

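### Poor tolerance is an absolute pain cut-off at 24, 48 and 72 h, with no pre-insertion score and no count of tubes removed for discomfort, so the calibre comparison is diluted and can favour the worst-tolerated tube

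*Protocol article*

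**What the plan says.** Section 1.3 (Secondary endpoint) lists tolerance of the tube models as a secondary outcome, measured as pain "evaluated through the NRS scale at 24-48-72 h after placement". It adds that "an NRS score greater than ≥3 will be considered as a threshold value to identify poor tolerance". I read the cut-off as 3 or more. It is a level, not a change from an earlier value.

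Section 2.2 (Study procedures) repeats the schedule: "Patient tolerance to the NGT will be assessed at 24, 48 72 h post-placement using the NRS scale". It also gives the purpose: "This will help identify pain levels and characteristics, to evaluate whether different NGT calibers (CH) affect patient tolerance".

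Three other places touch on the matter without altering the definition:

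- Section 2.2.7 states that "the patient's tolerance during the period of hospitalization will also be monitored", but names no instrument, time point or rule.
- Section 2.4 covers disposal of tubes "if they are removed after positioning during the hospitalization period". Removal is thus foreseen, but only as a waste question.
- Section 2.2.6 treats only the case in which the tube cannot be placed.

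Nowhere does the article give a score before insertion, make a score depend on the assigned tube being in place, or say how a tube removed before 24, 48 or 72 h counts.

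**The concern.** The endpoint is meant to show whether calibre affects tolerance, and Section 3 (Implications and Perspectives) says tolerability will help decide which tubes to recommend. Two features of the definition work against that.

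First, participants are inpatients who may have pain from other causes. With an absolute cut-off and no reference value, a patient already at the cut-off before insertion meets the definition of poor tolerance.

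Second, a patient whose tube is taken out at, say, 12 h because it could not be borne is the clearest tolerance failure there is. Under the stated rule that patient either gives scores with no tube in place or gives none. In neither case does the failure register as such. The more often a tube is removed early for discomfort, the fewer poor-tolerance scores it can collect.

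**Working it through.** **The plan's own figure.** The article gives no rate, standard deviation or difference for tolerance. Section 2.5.1 only asserts that the sample size is also enough to see a difference in discomfort. Its one worked figure, 47 per arm, belongs to the primary endpoint (42% versus 62%, power 80%, type I error 5%). It reproduces as a one-sample, two-sided comparison with a fixed 42%:

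n = [(1.96·√(0.42·0.58) + 0.842·√(0.62·0.38)) / 0.20]² = 47.3.

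No tolerance input enters it, so it does not settle the present point.

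**Assumptions for the illustration (none from the article).** Tube-related poor tolerance is 20% in one arm and 40% in another. Each arm has 50 patients (Section 2.5.1). The test is two-sided at 5% between two arms. Power uses the normal approximation with pooled variance under the null. With no disturbance the difference is 20 points and power is 59%.

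**(a) Background pain.** Let u be the share of patients at or above the cut-off for other reasons, equal in both arms and independent of tube pain. With t the tube-related rate, the observed rate is 1 − (1 − u)(1 − t), so the difference is (1 − u) × 20 points.

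| u | Observed rates | Difference | Power |
|---|---|---|---|
| 10% | 28% vs 46% | 18 points | 46% |
| 20% | 36% vs 52% | 16 points | 36% |
| 30% | 44% vs 58% | 14 points | 29% |
| 40% | 52% vs 64% | 12 points | 23% |

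Both absolute rates rise and the difference shrinks, but its direction is kept.

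**(b) Early removal.** Let f be the share of poorly tolerating patients in the worse arm whose tube is out before the first score, with none in the better arm and no background pain.

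- If they are scored without the tube and fall below the cut-off, the observed rate is 0.40(1 − f).
- If they are missing, it is 0.40(1 − f)/(1 − 0.40f).

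| f | Scored without tube | Missing | Difference from 20% |
|---|---|---|---|
| 10% | 36% | 37.5% | 16 or 17.5 points |
| 25% | 30% | 33.3% | 10 or 13.3 points |
| 50% | 20% | 25% | 0 or 5 points |

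If the same share f is removed in both arms and then scores below the cut-off, the difference is (1 − f) × 20, that is 18, 15 or 10 points. The shrinkage does not depend on removal being confined to one arm, but it is larger when it is.

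**Analysis populations.** Section 2.5.2 keeps every patient in the randomised arm for the intent-to-treat analysis and moves switched patients to the tube received in the per-protocol analysis. Neither rule registers removal or replacement for discomfort as a tolerance failure.

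**The case against.** The strongest reply has four parts.

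1. **Background pain does not bias a randomised comparison.** This stands. A reader might infer that the missing pre-insertion score makes the between-arm comparison invalid. It does not. The cost is inflated absolute rates and lost precision.

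2. **Insertion pain is a separate matter.** This also stands. The abstract says that "the study aims to evaluate patient tolerance to the intervention", and a reader might conclude that leaving the passage of the tube unscored is an error. Sections 1.3 and 2.2 fix the endpoint as the period after placement, which is a legitimate choice. Nor does the article show that insertion is when calibres differ most.

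3. **The article does not say that patients are scored after removal, and a condensed article may leave such handling to the full protocol, case report form or analysis plan.** The first half stands: it would be wrong to say that the plan classes removed patients as tolerating the tube well. The second half stands only in part. Time points and cut-off are fixed twice here, and under them an early removal is either a score without the tube or a missing score. Both lower the observed rate in the worse arm in the working above. The mention of pain characteristics in Section 2.2 and the general monitoring in Section 2.2.7 do not enter the threshold.

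4. **A finding of no difference could not support the remark in Section 3 that the new tubes add no burden.** Correct. That remark compares them with classical tubes, which are not an arm. What is at stake is the comparison among the three study tubes, including the hypothesis in Section 3 that smaller calibres cause less discomfort.

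**Conclusion.** The point holds as a weakness in how a secondary endpoint is defined, and the primary endpoint is unaffected. Pain unrelated to the tube counts as poor tolerance, which dilutes the difference between arms without biasing its direction. Early removal for discomfort is a consequence of the assigned tube that randomisation cannot balance, and leaving it uncounted can favour the worst-tolerated tube.

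The true size cannot be derived from the article. The losses shown rest on assumed tube-related rates of 20% and 40%, on background pain independent of tube pain, and, for the removal table, on removal in the worse arm only. If early removal for discomfort turns out to be rare, the second effect is small and only the dilution remains.

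**What to change.** These changes affect measurement and analysis only. The protocol's own cut-off stays.

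- Record one NRS score just before insertion, and adjust the between-arm comparison of tolerance for it.
- Record the date and reason of tube removal on the case report form.
- Define poor tolerance as reaching the protocol's NRS cut-off with the assigned tube in place, or removal of the assigned tube for discomfort before 72 h.

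The cost is one extra question, one extra form field and a composite endpoint. Reporting the two components separately would keep the composite readable. A pre-insertion score cannot be reconstructed later, so it should be in place before enrolment or added for the patients still to come. A further score right after insertion is optional and not needed for the endpoint as stated.
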